# A phase 2 quasi-experimental trial evaluating the feasibility, acceptability, and potential effectiveness of complex nursing intervention focused on QoL assessment on advanced cancer patients with palliative care needs: study protocol

**DOI:** 10.1186/s40814-017-0196-x

**Published:** 2017-11-13

**Keywords:** Quality of life, Complex intervention, Palliative care, Patient-reported outcome measure, Cancer patient, Outcome measurement, Outcome assessment, Development, Implementation, Nurse-led intervention, Nursing-sensitive patient outcomes, Patient-centered outcome measure

## Abstract

**Background:**

Palliative care (PC) is an approach that improves the quality of life (QoL) of patients and their families facing the problem associated with incurable terminal disease. A number of QoL assessment tools have been validated in PC and their use described for research purposes, to support clinical practice, and as part of the quality improvement programs. There is a paucity of evidence on the implementation of a nursing intervention focused on QoL assessment in PC practice.

The aim of this study is to model and determine the feasibility of a nursing complex intervention focused on QoL assessment in PC practice.

**Methods:**

The intervention will be evaluated through a quasi-experimental non-equivalent comparison group before-after study design. This project can be classified as phases 1–2, according to the Medical Research Council (MRC) framework for the development and evaluation of complex interventions.

The study setting will take place in two inpatient hospice units in Italy. The study sample will be constituted of 39 multidisciplinary healthcare professionals and a sample of 46 advanced cancer patients admitted to hospices during the implementation of the intervention.

**Discussion:**

This study will generate information to address the implementation of QoL measurement in palliative care practice. Findings of this study will be used to inform a phase 3 trial according to the MRC framework.

**Trial registration:**

ISRCTN41201864 retrospectively registered.

## Background

Although quality of life (QoL) assessment is a central concept in palliative care (PC) practice [1], the standardized application of clinical interventions focused on assessing QoL in clinical practice is limited. In addition, current research is insufficient to determine how to implement such interventions and determine their impact on patient outcomes [2, 3].

QoL has been described as the gap between individual’s expectations and their perception of a given situation [4], and its management entails the use of a QoL tool to screen and then monitor QoL changes over time. Recently, authors of a systematic review on facilitators and barriers to the successful implementation of Patient-Reported Outcome Measures (PROMs) in PC recommended tailoring this implementation according to the setting, having a coordinator throughout the implementation process, offering all staff an educational program, and recognizing the ongoing cognitive and emotional processes in each individual [5].

During the previous decade, a number of QoL measurement intervention components targeted at staff and practice in PC have been suggested such as choosing a tool, identifying a leader of the project, and staff training [6]. In addition, a European-funded research project—the PRISMA-FP7 project—introduced standards for the measurement of outcomes in PC [7], and more recently, an evidence-based clinical guidance on how to respond to patient-reported outcomes measurement in clinical care was proposed [8]. These initiatives indirectly emphasized both the inherent complexity of such interventions and the need for clinicians to respond to the patients’ complex needs. International scientific associations contribute to a growing body of guidelines claiming that QoL dimensions need to be comprehensively assessed and documented using available standardized scales [9].

In 2010, a systematic review conducted to determine the availability of PROMs to assess QoL in PC identified many measurement instruments and concluded that there was no agreement on how quality of life should be measured [10]. A subsequent systematic review evaluated to what extent interventions focused on QoL assessment improve PC patient outcomes revealed that overall implementation interventions focused on QoL assessment in PC practice do result in improved patient outcomes. Although included studies suffered from small sample size and selection, attrition, and performance bias, findings showed that such interventions can have a moderate practical significance on symptoms, psychosocial dimensions, and overall QoL [2].

Therefore, we designed an evidence-based intervention focused on QoL measurement in PC practice developed according to the Medical Research Council (MRC) framework for developing and evaluating complex interventions [11]. We are interested in understanding the feasibility of implementing the intervention in PC practice to inform the design of a phase 3 randomized controlled trial.

### Aims

The aim of the present study is to model and determine the feasibility of a nursing complex intervention focused on QoL assessment in PC practice and developed according to the MRC framework for developing, implementing, and evaluating complex interventions [11].

## Methods/design

Our study is designed to improve PC patients’ QoL (i.e., prevent/manage impaired QoL) during admission to an inpatient hospice unit. Flowchart of the entire intervention focused on QoL measurement (INFO-QoL) project and this study protocol (phases 1–2) are shown in Fig. 1
**.**

**Fig. 1 Fig1:**
[figure not shown]
Flowchart of the INFO-QoL study

### Operational definitions

For the purpose of this study, QoL was defined as the gap between a person’s life experience and expectations [4]. Addressing the problem (i.e., impaired QoL) begins by assessing patient’s QoL, and the information collected will serve as a basis to formulate realistic goals [7].

Our primary hypothesis is that patients, who will be cared for by hospice staff that have implemented a nurse-led complex intervention focused on QoL measurement, will have a significantly better QoL compared with patients cared for by staff that provide traditional care.

According to the MRC framework, the primary objective of the study is to model the INFO-QoL intervention (phase 1) and determine the feasibility, acceptability, and potential effectiveness of the INFO-QoL intervention (phase 2).

The secondary objective is to pilot methods for a phase 3 randomized controlled trial including sample size, the power of the study, recruitment, follow-up, suitability of measures, and documentations.

The research questions are the following:Are the procedures of the INFO-QoL conveniently performed as planned to yield information on patients’ needs within a reasonable time frame?Is the INFO-QoL acceptable to hospice staff and their patients?What is the potential effectiveness of the implementation of the INFO-QoL in terms of patients’ QoL and QoL-related management actions taken by PC staff per patient?

### Conceptual model

The study will be based on the conceptual model of *The QoL Assessment Principles in Palliative Care* developed according to phase 0 of the MRC framework. It consists of four sections, for a total of 11 principles to be considered in developing and/or evaluating clinical interventions focused on QoL assessment in PC. The model has been proposed as a methodological and ethical standard to be considered when developing and evaluating clinical interventions focused on QoL assessment in PC. Section one includes three principles related to “the problem” (i.e., a QoL impairment), section two includes two principles dealing with the assessment tool, section three includes one principle focusing on the treatment/intervention, and section four includes five principles dealing with “the clinical intervention focused on QoL assessment” [12] (Table 1).

**Table 1 Tab1:** The Qol assessment principles in palliative care

The problem (the Qol impairment)
1. The problem should be a serious condition for the patient either in terms of prevalence (e.g., pain, depression) and/or distress for the patient (e.g., itch, hiccup) or the result of late detection and management of the problem (e.g., a new or unusual distressing symptom occurred over the disease trajectory).
2. The problem should be highly unlikely to be reported by the patient or recognized by the professional if not actively assessed.
3. The trajectory of the problem should be sufficiently understood to assure a timely assessment to anticipate and appropriately address the problem.
The assessment tool
4. A validated, reliable, and sensitive-to-change tool for detecting and measuring the problem should be available.
5. The tool should be practical and easy to use, and questions must not be distressing for the patients.
The treatment-intervention
6. There should be an appropriate treatment/intervention for patients with the recognized problem.
The clinical intervention focused on Qol assessment
7. There should be an agreed policy on which a problem (or a problem with a certain degree of impairment) has to be addressed with appropriate treatment or intervention.
8. It should be possible for the tool to be appropriately administered by professionals trained in the procedure.
9. The treatment-intervention for patients with QoL impairments should be available, with appropriately trained professionals.
10. The cost of problem-finding (including all the steps from the administration of the tool until the treatment-intervention has been delivered in full) should be economically justified.
11. QoL assessment should be a continuing process rather than a one-off assessment.

Adapted from Catania et al. [12]

### Intervention design (theoretical phase)

The development of the INFO-QoL was carried out through several stages hereafter described (1) We conceptualized that any intervention focused on QoL assessment is a complex intervention and as such includes many components that form a coherent structure that links the intervention to patient’s QoL [12]. (2) We developed the conceptual model of *The QoL Assessment Principles in Palliative Care* by adapting the WHO Screening Principles framework [13] to QoL assessment in PC [12]. (3) We identified the components and the extent of the outcomes resulting from the interventions focused on QoL measurement by systematically reviewing the literature [2, 14]. (4) We identified the key elements that led to successful QoL measurement and then determined whether such components could be used in Italy by undertaking a study visit at St. Christopher’s Hospice in UK granted by the European Oncology Nursing Society (EONS) through the Clinical Travel Grant 2012. After asking the experts in the hospice, they emphasized that components such as staff education, measurement timeframe, designated person in charge of the process, and results discussed during unit staff briefing were the key elements they addressed before starting up QoL measurement [15]. Such components need to be locally adapted before their implementation in Italy. The final version of the INFO-QoL is described in Table 2.

**Table 2 Tab2:** The intervention focused on quality of life measurement

1. Name of intervention
The INtervention FOcused on Quality of Life Measurement (The INFO-QoL)
*2.* Goals of intervention
a. Ultimate goal: to prevent/manage impaired quality of life in advanced cancer patients with palliative care needs in hospice setting and promote measurement of patient’s quality of life b. Immediate goals: i. To reduce prevalence and/or severity of patient’ s problems/needs ii. To identify patients at risk of developing impairments in QoL dimensions iii. To increase staff awareness of problems/needs, their trajectory, and appropriate intervention to address them iv. To inform individual care plans based on impaired QoL dimensions and local policies
*3.* Components and activities
a. Component 1: ensure that treatment plans and evaluations focus on patient rather than disease i. Goal: to educate staff about QoL issues and about interventions that promote a better QoL ii. Activities: discuss the following topics: – What is QoL in palliative care patients? – What are the dimensions that contribute to a person’s QoL? – What are the determinants of changes in self-assessment of QoL? – How staff should propose, use, and score QoL tools to patients – How palliative care staff can effect changes in patients to improve their QoL b. Component 2: the Palliative Outcome Scale (POS) as an integral component of the intervention i. Goal: patient and family education on using outcome measures ii. Activities: present the purpose of QoL assessment to patients and their families; educate patients on using the POS c. Component 3: QoL measurement using the POS i. Goal: to promote cohesive, coordinated patient- and family-centered care ii. Activities: screening (i.e., baseline) and monitoring individual patients (morning shift), record individual and overall scores on individual INFO-QoL form, and discuss results to inform clinical decision during unit staff briefing
4. Mode of delivery
a. Component 1: small group education session (6–8 palliative care nurses) i. Use combination of written and verbal presentation and group discussion ii. Written presentation: case-based materials, self-study binders, poster iii. Verbal presentation: evidence on QOL issue in palliative care iv. Group discussion: elicit case discussions to focus on issues related to patients’ QoL b. Component 2: nurses-patient and family face-to-face interaction i. Use combination of written material and verbal communication ii. Written materials, such as handout on QoL issues, and poster with large print and simple language hanging in the inpatient hospice unit iii. Verbal communication using a slow rate of speech, simple and common words, short sentences, and a teach-back technique c. Component 3: individual QoL measurement i. Nurse team leader is responsible to manage the measurement (i.e., schedule the measurement, prepare documentation, assign patient to nurse or nursing assistant, oversee completion of QoL measurement) ii. Nurse or nursing assistant who perform the QoL measurement motivates patient to improve compliance iii. Staff discusses results and gives feedback of results and care plan to patient
5. Dose
a. Component 1: self-study binders given 2 weeks before the education bundle program session; one small group education session of 3-h duration (repeated at different time points to allow all staff to participate) b. Component 2: education session of about 10/15-min duration c. Component 3: measurement within day 3 from admittance, days 8–10, day 15 and then once a week; patient feedback at the same day of the measurement

### Study population

The study will be conducted on a convenience sample of two hospice units of the urban district of Genoa in the north of Italy: the Gigi Ghirotti Bolzaneto Hospice is a 12-bed nonprofit hospice (Gigi Ghirotti Hospice—Association for Research and Treatment of Pain and Palliative Care), and the Maria Chighine Hospice is a 12-bed public hospice (IRCCS AOU San Martino—IST—Teaching Hospital and Cancer Research Centre). In both of these hospice units, healthcare professionals were educated and trained in PC and communication in end-of-life care and are using the Liverpool Care Pathway [16]. According to the definition of the European Association for Palliative Care, “they admit patients in their last phase of life when treatment in the hospital is not necessary and care at home or in nursing home is not possible” [17]. The National Health System covers all or part of the costs of the care for the public and nonprofit hospice, respectively. The hospice staff of the Ghirotti Hospice includes 1 physician, 10 nurses, and 6 nursing assistants, and the Maria Chighine Hospice includes 3 physicians, 12 nurses, and 7 nursing assistants.

The sample will consist of all the PC team members within the two hospices during the modeling and feasibility phase. During the 6-month period of the feasibility phase (pre-test = 3 months; post-test = 3 months), all adult cancer patients newly admitted to the hospice units will be invited to participate in the study and they will be included after giving their informed consent. Patients too ill to receive the intervention or unable to give informed consent either due to cognitive impairment or because they are unable to understand Italian will be excluded.

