### The exploratory trial (assessing feasibility and piloting method)

As the INFO-QoL is being implemented throughout the unit and it will be difficult to deliver the intervention randomly to some patients but not to others, the feasibility stage will have a quasi-experimental non-equivalent comparison group before/after design. Although randomized controlled trials represent the gold standard, and quasi-experimental designs have a weakened confidence in making causal assertions that the results occurred because of the intervention, quasi-experimental designs can also provide useful information to establish whether (and to what extent) an intervention is effective. A non-equivalent comparison group design is the strongest of the quasi-experimental designs and can provide good evidence for nursing practice. Quasi-experimental designs are more feasible and more commonly conducted for nursing studies in clinical settings. This design will enable the researcher to pilot the components and methods and the feasibility of the INFO-QoL, in order to assess its acceptability in practice and determine whether the INFO-QoL is delivered according to the study protocol. It will also offer the opportunity to determine potential effectiveness of the INFO-QoL in improving patient QoL.

To partially address selection bias, the INFO-QoL described in Table 2 will be introduced randomly into unit 1 (intervention unit), while patients and staff in unit 2 (comparison unit) will continue with traditional clinical practice. By gathering pre-test data, we can compare the equivalence of the two groups on antecedent variables before introducing of the independent variable [25]. The study will inform methods for the future phase 3 trial in determining sample size and the power of the trial, recruitment, follow-up, and suitability of measures. For the purpose of this study, the type and quality of care delivered by sites will not be assessed: it will be assumed to be at least comparable between the two hospice units.

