### Randomization

The unit of randomization is the hospice unit. To prevent performance bias before randomly allocating the experimental intervention in one of the two units, the collection of pre-test data will occur within a three-month period in both units before making any change. Subsequently, to reduce the selection bias, the INFO-QoL will be implemented randomly in “unit 1” (intervention unit), while patients and staff in the “unit 2” (comparison unit) will continue with the standard clinical practice.

Randomization will be performed independently by using a computer-generated sequence. The randomization procedure will be centralized and managed by an independent statistician at the coordinating center of the study. All study investigators, personnel, and participants will be unaware of the randomization procedure.

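### The exclusion for being too ill to receive the intervention is tied to something delivered in only one of the four unit/period groups, so it may select somewhat fitter patients there

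*Protocol article*

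**What the plan says.** Study population recruits over two periods, "pre-test = 3 months; post-test = 3 months", during which "all adult cancer patients newly admitted to the hospice units will be invited to participate in the study". It then gives one exclusion rule for the whole phase: "Patients too ill to receive the intervention or unable to give informed consent", the latter because of cognitive impairment or language.

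Randomization states that "the collection of pre-test data will occur within a three-month period in both units before making any change" and that afterwards "the INFO-QoL will be implemented randomly in “unit 1” (intervention unit), while patients and staff in the “unit 2” (comparison unit) will continue". The INFO-QoL is thus present in one of four unit/period groups: unit 1, post-test.

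Table 2 describes what a patient receives under the INFO-QoL: an education session of roughly 10 to 15 minutes with teach-back, the POS measurement itself (Component 3), and feedback on the same day. Potential effectiveness has the POS given in both units and both periods at T0, T1 and T2, with a completion time of 7 minutes, and compares scores before and after and between units.

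Against selection bias, the section on the exploratory trial offers random choice of the intervention unit and a baseline check: "By gathering pre-test data, we can compare the equivalence of the two groups on antecedent variables".

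**The concern.** The threshold for being too ill refers to the demands of the INFO-QoL. Where it is delivered, a screener has a real session and a real feedback conversation in mind. In the other three groups the patient faces only consent and the POS. If the rule is judged against what the patient will actually undergo, the bar is higher in unit 1 post-test than elsewhere.

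Patients are not randomised and the units are acknowledged to be non-equivalent, so the unit-by-period contrast relies on selection working the same way in all four groups. POS items run from 0 (no problem) to 4 (overwhelming). If sicker patients score higher, removing some of them from one group alone lowers its mean and looks like benefit. Potential effectiveness is part of the primary objective, and the results are meant to inform a phase 3 trial.

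**Working it through.** **1. Is the demand different?** Consent and the POS are common to all four groups. The education and the feedback belong to unit 1 post-test only. The patients at issue can manage the first two but not the last two.

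**2. Would the stated safeguards catch a shift?**
- The equivalence check uses pre-test data, collected before the INFO-QoL exists in either unit. It cannot show a difference that begins post-test.
- Before/after differencing does not remove it. If the unit 1 post-test mean moves by δ, the contrast (unit 1 post − unit 1 pre) − (unit 2 post − unit 2 pre) also moves by δ.
- Randomization says study personnel and participants are unaware of the randomization procedure, which is not the same as the allocation. The blinded research assistant under Potential effectiveness is specified for giving the POS in the comparison unit, not for judging eligibility.
- Post-test T0 scores could show part of a shift. In unit 1, however, the T0 POS is itself Component 3 and may follow the Component 2 education, so it is not a clean baseline.

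**3. Benchmark.** Sample size plans for an effect of 0.3 SD with 17 patients per unit/period. The one-sided 80% half-width for two groups of 17 with SD 1 is t(0.80, 32) × √(2/17) = 0.853 × 0.343 = 0.293. This is below 0.3, so 17 is consistent with that benchmark. (The distance of 0.200 also stated there does not follow from n = 17. That is a separate matter and is not used here.)

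**4. Possible size.** The document gives neither the extra share excluded (q) nor the correlation between illness and POS (r), so both are assumed. If the sickest share q is removed from one group only, the mean POS shift in SD units is

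r × f(q), with f(q) = φ(c)/(1 − q) and c = Φ⁻¹(1 − q).

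| q | f(q) | r = 0.3 | r = 0.5 | r = 0.7 |
|---|---|---|---|---|
| 5% | 0.109 | 0.033 | 0.054 | 0.076 |
| 10% | 0.195 | 0.058 | 0.097 | 0.136 |
| 20% | 0.350 | 0.105 | 0.175 | 0.245 |

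At 5 to 10% the range is 0.03 to 0.14 SD, or 0.033/0.3 = 11% to 0.136/0.3 = 45% of the planned effect.

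**5. Allowing for exclusions shared by all groups.** Needing to consent and complete a POS already removes some of the sickest everywhere. If a share p is excluded in every group, the shift becomes r × [f(p + q) − f(p)].
- p = 10%, q = 5%: f(0.15) − f(0.10) = 0.274 − 0.195 = 0.079, giving 0.024 to 0.056 SD.
- p = 10%, q = 10%: 0.350 − 0.195 = 0.155, giving 0.046 to 0.108 SD.
- p = 20%, q = 5%: 0.424 − 0.350 = 0.074, giving 0.022 to 0.052 SD.
- p = 20%, q = 10%: 0.497 − 0.350 = 0.147, giving 0.044 to 0.103 SD.

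With shared exclusions the range for 5 to 10% extra is therefore about 0.02 to 0.11 SD.

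**The case against.** The rule can be read as a common criterion. It is stated once, for both units and both periods, including a pre-test period in which no unit has been allocated. Table 2 describes the intervention, so a screener anywhere could judge a patient against it. This reading is available and a careful team might follow it. The text does not require it, however, so the risk remains.

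The margin for differential exclusion is narrow. Every patient must be able to discuss an information sheet, sign consent and complete the POS, which is itself one of the three components. The education session is short and designed for frail people. This stands, and it is why the size is kept modest.

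The magnitude is assumed throughout. With a POS alpha of 0.65, an observed correlation of 0.7 implies 0.7/√0.65 = 0.87 after correcting for unreliability, which is high for a scale that also covers psychological and spiritual items. The standard error with 17 per group is √(2/17) = 0.34 SD for two groups and √(4/17) = 0.49 SD for four, so a shift of 0.03 to 0.14 SD is small beside sampling error. This also stands. Bias, unlike sampling error, does not shrink with more patients, and this study's estimate is meant to feed a larger trial.

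The protocol concedes that its design weakens causal claims. That is fair, but it does not argue against removing an avoidable source of bias by changing one sentence.

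**Conclusion.** The point holds as a possible, avoidable source of differential selection. The criterion depends on an intervention present in one of four groups, nothing stated forces uniform application or an assessor unaware of allocation, and the pre-test check cannot detect the result. Under the assumed r of 0.3 to 0.7 and 5 to 10% extra exclusion, the spurious improvement is about 0.03 to 0.14 SD against 0.3 SD, and somewhat less if consent and POS capacity already exclude patients everywhere.

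Three stronger readings are not supported. A reader might infer that the rule operates in one group only; the text states it for all, and its application elsewhere is merely unspecified. A reader might infer that unblinded staff make the eligibility decision; the article does not say who does. A reader might take 0.245 SD, about four fifths of the planned effect, as the likely size; that needs both 20% extra exclusion and a correlation of 0.7, and the document gives no basis for either.

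The direction towards the intervention applies to comparisons of POS scores. If change from T0 were analysed, it would be uncertain.

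**What to change.** Replace the criterion with one that does not depend on allocation, for example judged able to give consent and to complete a POS of about 7 minutes. Assess it at admission, before any INFO-QoL activity, and apply it identically in both units and both periods. The timing matters: in unit 1 post-test, patients are taught to use the POS and nurses encourage completion, so actual completion at T0 could itself differ by unit.

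Keep enrolled unit 1 patients who cannot complete the education or feedback in the analysis, and record them as fidelity and feasibility data. The staff checklists under Feasibility of intervention already provide for deviations and uncompleted measurements. Report the number excluded for illness by unit and period.

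The cost is one sentence in the eligibility criteria and one tabulation. The planned number per unit/period does not change. The small downside is that some unit 1 patients will not receive the full intervention, which slightly dilutes the effect but is itself a feasibility result.
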